## Abstract

**Background:**

The successful recruitment and retention of health professionals to rural and remote areas of Australia is a health policy priority. Nursing or allied health professional students’ learning placements in the Northern Territory (NT) of Australia, most of which is considered remote, may influence rural or remote work location decisions.

**Objective:**

The aim of this study is to determine where allied health professionals and nurses who have had a student placement in the NT of Australia end up practicing.

**Methods:**

This research is an observational cohort study, with data collection occurring at baseline and then repeated annually over 10 years (ie, 2017-2018 to 2029). The baseline data collection includes a demographic profile of allied health and nursing students and their evaluations of their NT placements using a nationally consistent questionnaire (ie, the Student Satisfaction Survey). The Work Location Survey, which will be administered annually, will track work location and the influences on work location decisions.

**Results:**

This study will generate unique data on the remote and rural work locations of nursing and allied health professional students who had a placement in the NT of Australia. It will be able to determine what are the most important characteristics of those who take up remote and rural employment, even if outside of the NT, and to identify barriers to remote employment.

**Conclusions:**

This study will add knowledge to the literature regarding rates of allied health and nursing professionals working in remote or rural settings following remote or rural learning placements. The results will be of interest to government and remote health workforce planners.

**Trial Registration:**

Australian New Zealand Clinical Trials Registry (ANZCTR) ACTRN12620000797976; https://www.anzctr.org.au/ACTRN12620000797976.aspx

**International Registered Report Identifier (IRRID):**

PRR1-10.2196/21832

## Introduction

### Background

Australia’s population predominately lives in its major cities (72%), with another 26% living in regional areas and just 2% living in remote or very remote areas [1]. However, 73% of the Australian landmass is considered *very remote* and a further 13% as *remote* [2], with the *outer regional* and *inner regional* categories respectively covering 11% and 3% of Australia’s land area. The Northern Territory (NT) of Australia is one of the least densely populated areas in the world, with 0.16 people per square kilometer, compared to the overall Australian rate of 3.3 people per square kilometer, 4.1 people per square kilometer in Canada, and 36 people per square kilometer in the United States [3].

The health status of residents in rural and remote Australia is well-known to be worse than that of residents of major cities. Chronic disease and mortality rates are higher and access to health services are poorer [4]. One of the key factors that influences access to health services in rural and remote Australia is the ability to recruit and retain skilled and qualified clinicians [5-8]. There is a maldistribution and shortage of the health workforce, with a lack of health professionals outside major centers being one of the reasons often cited for lower health outcomes of remote and rural Australians. In addition, practicing as a health professional in remote areas is significantly different from practicing in metropolitan centers [9,10]. However, frequently, the curriculum in health professional training programs pays scant attention to preparing students for remote practice [11-13].

The NT has the highest proportion (approximately 30%) of Indigenous residents in Australia, with many living in remote and very remote locations. Aboriginal Australians also carry a higher burden of disease and have greater challenges in accessing health services [14].

The National Strategic Framework for Rural and Remote Health [2] workforce profile demonstrates the difficulties for rural and remote residents in accessing health professionals. For example, it estimates that in rural and remote Australia there are 589 registered nurses per 100,000 population compared to 978 per 100,000 in major cities, and only 64 allied health workers per 100,000 population compared to 354 per 100,000 in major cities [2]. Internationally, the value of the health workforce and the need to significantly increase it has been recognized by the World Health Organization [15].

Undertaking workplace-based learning placements is foundational throughout health professional training programs [16]; in addition, there is a growing body of literature from Australia, Canada, and New Zealand on the value of quality student placements in rural and remote areas and the ways in which placements might positively influence recruitment and retention [17-20]. The successful recruitment and retention of health professionals to rural and remote areas has also become a focus of current health policy. The Australian Commonwealth Government introduced Rural Health Multidisciplinary Training (RHMT) Expansion Program funding in 2016 with a specific focus on nursing and allied health professions. The RHMT Program is designed to encourage the recruitment and retention of rural and remote health professionals by “supporting effective rural training experiences” for health students [21].

Research into the effects of undertaking placements in rural and remote areas and students’ intentions to return to take up positions after graduation has found a positive association between exposure to rural practice and the intention to consider working in a similar situation [7,22-29]. One study also found a positive relationship between rural exposure and return to rural practice, even among those who had taken up positions in a metro area: “there did seem to be a widespread disposition to working in rural areas...even if they were not currently doing so” [30]. Critically, however, there is little known about how intention translates into the uptake of positions in rural and remote places over time.

The career decisions that early-career health professionals make are influenced by a range of factors (eg, [31-34]). Many of these, such as family location and personal career goals, are beyond the control or influence of universities and workplaces. Equally important, the quality of placements in rural and remote areas can be directly influenced by the work of the RHMT Program and the support provided to students, workplaces, and supervisors [29]. The impact of large-scale but locally delivered placement support on long-term remote career location decisions by nursing and allied health professional students has not been investigated.

Internationally, there are relatively few studies on the effects of rural or remote health placements on allied health professionals’ decisions to work in a remote setting. The bulk of the literature regarding work location outcomes focuses on medical students, with most studies reporting that an “organised, well-funded, rural placement or rural clinical school program produced positive associations with increased rural intentions and actual graduate rural employment” [35]. Considerable work also focuses on challenges associated with remote nursing [36].

### Context

Flinders University in Adelaide, Australia, has a long history of delivering education and training to develop the Australian NT health workforce [37,38]. In 2016, Flinders University was awarded a national federal government grant, the RHMT Expansion Program, to provide NT-wide support for work-integrated learning placement students from nursing and allied health professions. The grant encourages rural and remote placements as a strategy for recruitment of health professions to the rural and remote workforce. To evaluate the effectiveness of this program, the planned study will track the career location decisions of former placement students and explore the impact of their NT placements on their work choices.

This research is a 10-year tracking study of the work practice locations of all nursing and allied health students who complete an NT work-integrated learning placement. The study will also investigate the factors that contribute to the work location decisions of the participants and will determine if and how an NT placement influenced career decision making.

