### Research Question and Objectives

The overarching research question for this study is as follows: Where do nursing and allied health professionals who have had a student placement in the NT end up practicing? The primary objective of this study is to identify the workplace locations, annually, of nursing and allied health students who completed an NT work-integrated learning placement; this will be conducted for 10 years postgraduation. The secondary objectives of this study are as follows: (1) investigate factors that contribute to work location decisions and (2) determine if and how an NT placement influenced career decisions.

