## Methods

### Theoretical Framework and Study Design

The research will use a pragmatist theoretical framework [39-41]. This research is an observational cohort study with data collection occurring at baseline and repeated annually over 10 years, from 2017-2018 to 2029 (see Table 1). The baseline data collection includes a demographic profile of nursing and allied health students and their evaluations of their NT placements (ie, Survey 1: Student Satisfaction Survey). The Student Satisfaction Survey is used nationally by University Departments of Rural Health across Australia [42]. The annual survey (ie, Survey 2: Work Location Survey) has been purpose developed to track work location and the influences on work location decisions.

**Table 1 table1:** Study design showing timing of recruitment and data collection.

Participant cohort	Study activity by year				
	2020	2021	2022	2023-2028	2029
Retrospective recruitment of 2017-2019 students (Cohorts 1-3)	Access to Flinders University Northern Territory (NT) database of completed placements Recruit and obtain consent using last known phone number and email address Survey 1^a^: already undertaken as part of routine quality assurance Survey 2.1^b^	Survey 2.2	Survey 2.3	Survey 2 taken annually up to and including 2026 for Cohort 1 and up to and including 2027 for Cohort 2	Completed
Recruitment of 2020 students (Cohort 4)	Access to Flinders NT database of commencing placements Recruit and obtain consent when sent Survey 1	Survey 2.1	Survey 2.2	Survey 2 taken annually up to and including 2028	Completed
Recruitment of 2021 students (Cohort 5)	N/A^c^	Access to Flinders NT database of commencing placements Recruit and obtain consent when sent Survey 1	Survey 2.1	Survey 2.2	Survey 2 taken annually until 2029 Cohort 5 tracked for 8 years in the workforce
Recruitment of 2022-2027 students (Cohorts 6-11)	N/A	N/A	Access to Flinders NT database of commencing placements Recruit and obtain consent when sent Survey 1	Survey 2.1	Survey 2 taken annually until 2029 Cohort 6 tracked for 7 years in the workforce Cohort 7 tracked for 6 years in the workforce Cohort 8 tracked for 5 years in the workforce Cohort 9 tracked for 4 years in the workforce Cohort 10 tracked for 3 years in the workforce Cohort 11 tracked for 2 years in the workforce
Recruitment of 2028 students (Cohort 12)	N/A	N/A	N/A	Access to Flinders NT database of commencing placements Recruit and obtain consent when sent Survey 1	Survey 2.1

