### Participants and Eligibility

Study participants will be students or graduates, over the age of 18 years, of an Australian allied health or nursing training program and will have undertaken an NT placement as a student. Their placement, including any assessment of competence, will be concluded by the time of participation. Individuals who were already employed as a nursing or allied health professional and undertaking a placement as part of a postgraduate qualification will be excluded.

Framed by our pragmatist approach and as part of our due diligence around appropriate research designs, we considered using Australian Health Practitioner Regulation Agency (AHPRA) registration data rather than participant survey data. However, only about half of the professions of interest are registered through the AHPRA: Aboriginal and Torres Strait Islander Health Practitioner, Chinese medicine, chiropractic, dentistry, medical radiation, nursing and midwifery, occupational therapy, optometry, osteopathy, pharmacy, physiotherapy, podiatry, and psychology. Disciplines that are not registered include audiology, dietetics and nutrition, disability, exercise physiology, medical laboratory science, orthotics and prosthetics, paramedicine, social work, and speech pathology. Therefore, relying on AHPRA data to answer our primary question will not provide coverage of all the professions of interest.

The research design relies on access to the contact details of health professional students known to have undertaken work-integrated learning placements in the NT from 2017 onward. Flinders NT holds a secure database with the contact details of the placement students. These details were obtained for the purpose of supporting the placement; however, students consent to the use of their information for educational research purposes, such as our standard quality-improvement Student Satisfaction Survey regarding placement. Access to the database will allow the researchers to recruit participants to the study by contacting current and former students and inviting them to participate in the research.

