### Student Training and Placement

In this study, the intervention is having undertaken a student placement in the NT of at least one week in length. As part of standard accreditation processes, university-level health professional courses are required to demonstrate graduate competence in the application of knowledge and skills to patients and consumers of health care. Workplace-based placements, sometimes known as work-integrated learning activities, are a cornerstone of the curriculum because the students are working in health care workplaces under the supervision of a qualified health professional, learning to deliver the graduate competencies of the profession [43,44].

The supervision requirements, length, curriculum, and assessment of student placements vary according to the needs of the specific profession [12]. Whether the university pays the workplace or the workplace supervisor for providing the placement also varies. We recognize that the intervention includes student placement experiences that are not homogenous. From the perspective of workplaces, it is commonly assumed that student placements are a mutually beneficial recruitment strategy, allowing both the workplace and the student to consider the suitability and attractiveness of employment once they graduate [23,24,27,42,45].

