## Discussion

The question of how many allied health and nursing students, as well as their characteristics, who have had a remote student placement go on to work remotely is a gap in the literature on remote work locations, which more typically focuses on medical students and to a lesser extent on nursing students. Filling this gap is important, given the federal funding invested in the RHMT Expansion Program as a strategy to grow a local remote health workforce. Given the national policy priority to recruit and retain health professionals in remote and rural areas, new insights into strategies to achieve this are needed. It is recognized internationally that building a remote and rural health workforce is a common challenge [48].

The analyses will be able to determine what are the most important characteristics of those who take up remote and rural employment, even if outside the NT, while adjusting for potential confounders, and will identify independent barriers to remote employment. A meta-synthesis of recruitment and retention of occupational therapists and physiotherapists in rural areas found that the availability of, and access to, practice supports; opportunities for professional growth; and an understanding of the context of rural practice were important [20]. Further, the calculation of the proportion of students who have had a placement in a remote setting and went on to work remotely is important for workforce planning. One study reported that 1 year after graduation, half of the allied health students who had had a rural placement were working in a rural or remote location, compared to 23.7% of all graduates from these disciplines [49]. It remains to be determined what proportion of students undertaking a remote placement will be working in a remote location in the short, medium, or long term after graduation.

The very low population density in the NT makes it a unique context to study remote health workforce issues. How the factors influencing the selection of remote health workplace locations compared to rural settings needs further study.

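### The protocol says it will evaluate program effectiveness and determine whether an NT placement influenced careers, but everyone enrolled had the placement and no comparator is planned, so a placement effect cannot be estimated

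*Protocol article*

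**What the plan says.** **Purpose and aims.** The Context section, after describing the federal grant, states: "To evaluate the effectiveness of this program, the planned study will track the career location decisions of former placement students". The same section adds that the study will determine *if* and how the placement shaped career decisions. Under Research Question and Objectives, the primary objective is to "identify the workplace locations, annually, of nursing and allied health students who completed an NT work-integrated learning placement", and the second of the two secondary objectives is to "determine if and how an NT placement influenced career decisions".

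**Exposure.** Student Training and Placement says "In this study, the intervention is having undertaken a student placement in the NT of at least one week in length". Under Participants and Eligibility, those enrolled "will have undertaken an NT placement as a student".

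**Design and analysis.** Theoretical Framework and Study Design says "This research is an observational cohort study with data collection occurring at baseline and repeated annually over 10 years". Table 1 lists twelve cohorts, distinguished only by year of placement. Data Analysis plans descriptive summaries, a comparison of responders with nonresponders, an analysis of changes in work location, and a logistic regression of factors associated with working in MMM 4 to 7 rather than MMM 1 to 3.

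**Discussion.** Another study's result is cited: one year after graduation, half of allied health students with a rural placement worked rurally or remotely, "compared to 23.7% of all graduates from these disciplines". The limitations paragraph covers low participation and who chooses to respond. It does not mention the absence of a comparison group or self-selection into NT placements.

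**The concern.** Effectiveness, and the *if* in objective 2, are questions about a difference: what these graduates did against what they would have done without the placement. A cohort in which everybody received the intervention observes only the first half.

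Selection makes this more than a formality. The protocol collects rural origin and NT residency at baseline, so it expects participants to differ on both. If students who go to the NT were already more inclined to rural work, a high rural or remote proportion would appear even if the placement did nothing. The Discussion links the work to the federal investment in the program. A proportion presented under an effectiveness heading could therefore be taken as evidence that the funding worked, when the study cannot separate a placement effect from who went.

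**Working it through.** **1. The plan's own figures (Sample Size section).**
- First year: 3 × 450 × 0.15 = 202.5; stated 203.
- Pool: 12 × 450 = 5400, as stated.
- Final sample: the cumulative pool (1350, 1800, …, 5400) times the yearly response rate (0.15, 0.14, …, 0.06) gives 202.5 + 252 + 292.5 + 324 + 346.5 + 360 + 364.5 + 360 + 346.5 + 324 = 3172.5; stated 3175.

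The figures reproduce, the last as a sum of yearly survey responses. The point here does not depend on them, because the obstacle is not precision.

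**2. What is needed and what is observed.** Let p1 be the probability of rural or remote work among placement students, and p0 the probability for the same people had they had no placement. The effect is p1 − p0.
- p1 can be estimated from the annual survey, subject to nonresponse.
- p0 has no source. Eligibility excludes anyone without an NT placement, Table 1 has no other cohort, and Data Analysis names no historical group or external benchmark.

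With p0 free between 0 and 1, the effect can lie anywhere from p1 − 1 to p1. For illustration, assume p1 = 0.50. If p0 = 0.40 the effect is 0.50 − 0.40 = 10 points; if p0 = 0.50 it is 0. Nothing in the plan distinguishes these cases, and more responses sharpen p1 only.

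**3. The logistic regression.** Write logit P(MMM 4 to 7) = b0 + b1·placement + other terms. Placement equals 1 for every participant, so b1 cannot be separated from b0. Adjusting for confounders among placement students does not supply outcomes for people without a placement.

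**4. The comparisons that are planned.** Responders against nonresponders addresses representativeness. MMM 4 to 7 against MMM 1 to 3 is a contrast of outcome categories. Neither is a contrast of placement with no placement.

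**5. Could the 23.7% stand in for p0?** It is background from another study. As cited, it refers to all graduates of the allied health disciplines concerned, not to those without a placement, and not to nurses. The article does not say whether it used this study's outcome rule, which counts any service in MMM 4 to 7, full or part time, in the previous 12 months.

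**The case against.** The strongest reply is that this is a descriptive study with one loose phrase. The overarching question is where these graduates end up practicing, and the primary objective needs no control group. The effectiveness wording appears once, in Context, and is given content there as tracking locations. The Work Location Survey was developed to ask about influences on location decisions, so objective 2 can be read as reported influence. Much of this stands: the primary objective is sound, and perceived influence is answerable by self-report. It does not clear the text, because evaluating effectiveness and determining *if* an influence existed are still stated as aims, and the limitations do not qualify them.

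A reader might infer more than the protocol supports:
- *That rural origin and NT residency will only be described.* Data Analysis lists them under descriptive analysis, but it also plans a regression without naming covariates, and the Discussion promises confounder adjustment. They may well be in the model.
- *That a comparison with 23.7% is planned.* It is not; no benchmark test appears in Data Analysis.
- *That the bias from selection can be put at a number of percentage points.* The protocol gives neither the share of placement students with a rural or NT background nor rural uptake by background, so any such figure would rest wholly on assumptions.
- *That intention before the placement is unmeasured.* Baseline does follow the placement, but the questionnaires are not shown, and Data Analysis mentions influences on placement.

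**Conclusion.** The point holds for the effectiveness statement in Context and for the *if* in secondary objective 2. Eligibility and Table 1 fix an all-exposed cohort, so the effect of placement against no placement cannot be estimated from this study, whatever the sample size or analysis plan. This conclusion rests on the stated design alone and needs no assumed rates. No size can be put on any resulting bias from this document.

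It does not extend to the primary objective, to *how* participants say the placement influenced them, or to associations among placement students, provided these are presented as associations. The claims and the limitations need correcting; the descriptive study stands.

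**What to change.** 1. In Context, replace the effectiveness wording with a statement that the study describes work locations after an NT placement.
2. Reword secondary objective 2, and the matching sentence in Context, as describing participants' self-reported influence of the placement on work location.
3. Report the rural or remote proportion overall and separately by rural origin and by NT residency, and name both as covariates in the logistic regression. Both are already collected at baseline.
4. Add to the limitations that there is no comparator, that self-selection into NT placement is possible, and that no causal contrast is made with graduates who had no placement, including through the 23.7% figure.
5. Report any relation with placement length or number as association only. The protocol says length varies with the needs of the profession, and keener students may choose longer or repeat placements.

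The cost is a few sentences and one stratified table from existing variables, with no new data collection. The downside is a more modest claim about the program.
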